#### Phone Follow-Up Survey

For women who either moved out of Lilongwe or did not visit the Good Health Kauma Clinic, the field team attempted to contact them by phone up to a maximum of 3 times. Women who were reachable by phone were invited to participate in a short phone follow-up survey. To maintain a respondent’s privacy during an attempt to reach her by phone, the field enumerator conducting the call left no indication of the reason for the phone attempt (eg, voicemail, SMS text message) on the respondent’s phone if there was no response to a call. The phone follow-up survey instrument took no more than 20 minutes and was identical to the clinic-based follow-up survey instrument.

#### Home-Based Survey

For women who did not visit the Good Health Kauma Clinic and who were also uncontactable by phone, the field team attempted to contact them at their homes up to a maximum of one time. Women who were reachable at their homes were invited to participate in a home-based follow-up survey, which was administered in person by a field enumerator. The home-based follow-up survey instrument took no more than 20 minutes in total and was identical to the clinic-based and phone-based follow-up survey instruments. The survey was administered in a private room at a woman’s home.

All protocols related to the consent process and in-person survey administration followed during the baseline survey were also followed for the clinic, phone, and home surveys. Before administering each survey, the field enumerators clearly explained the purpose of the follow-up to the respondents and asked for their consent to participate. For in-person clinic-based and home-based surveys, written consent from respondents was solicited, whereas verbal consent was obtained from participants who were contacted for the phone survey. Following the receipt of consent, the enumerators would then ensure the confidentiality and privacy of responses by asking the respondent to find a private room or space in their household (for the baseline, counseling, phone follow-up, and home follow-up surveys) or at the clinic (for clinic-based surveys) where their responses could not be overheard. For each woman, survey data were collected up to a total of 3 time points (at baseline, at the counseling stage, and at the follow-up stage).

### Participant Compensation

All women who participated in the study received a small token of appreciation (3 bars of soap, a monetary equivalent of MWK 500 [US $0.66]) after completing the baseline survey. No monetary compensation was provided to participants for participating in the study, which served to minimize coercion. Participants were not informed of these tokens until the baseline survey had been administered.

All participants received a mobile phone credit of MWK 100 (US $0.14) by means of a mobile airtime transfer. To avoid coercion into participation, women were not informed of this airtime transfer until after the counseling session had been administered.

### Primary Outcomes

Key primary outcome variables include the following:

Attitude or knowledge of family planning, including knowledge of family planning and perceptions toward contraception (eg, intentions to use)Contraceptive use, including changes in contraceptive use, changes in method mix, and adherence to methods (compliance, switching, and discontinuation)Contraceptive preferences, including the ideal contraceptive method and the most valued contraceptive method attributePregnancy and fertility outcomes, including pregnancy status, parity, delivery in a facility, months since last birth, wantedness of last birth, and intentions to become pregnant in the futureUse of local health facilities, including the frequency of visits to local clinics and frequency of receipt of family planning counseling servicesHusband’s preferences, including the approval of family planning and fertility preferencesWomen’s autonomy, empowerment, and decision making

### Secondary Outcomes

A range of secondary outcomes were collected in each survey wave: (1) women’s education, employment, work, and income; (2) household assets; (3) postpartum treatment from last birth; (4) sexual and marital well-being; (5) husband’s employment, work, education, and earnings; (6) household bargaining and women’s autonomy and empowerment; and (7) trust in local health facilities. Outcomes were collected according to the schedule outlined in Table 3. All survey instruments (baseline, counseling, and follow-up) and intervention monitoring tools to track participants and intervention uptake over the course of the study are available upon request.

**Table 3 table3:** Outcome measures and instruments.

Outcome or instrument	Baseline	Counseling	Follow-up
Attitude or knowledge of family planning	✓^a^	✓	✓
Contraceptive use	✓	✓	✓
Pregnancy and fertility outcomes	✓	✓	✓
Contraceptive preferences	✓	✓	✓
Use of local health facilities	✓	—^b^	✓
Husband’s preferences, approval of family planning, and fertility preferences	✓	✓	✓
Women’s autonomy, empowerment, decision making, and household bargaining	✓	✓	✓
Women’s education, work, income, and employment	✓	✓	—
Household assets	✓	—	—
Postpartum treatment from last birth	✓	—	—
Sexual and marital well-being	✓	—	—
Husband’s employment, work, education, and earnings	✓	✓	—
Trust in local facilities	✓	—	✓
Spillover of the intervention between treatment groups	—	—	✓

^a^The outcome was collected in the survey wave.

^b^Not available. The outcome was not collected in the survey wave.

### Survey Instruments and Monitoring Tools

A paper version of the baseline survey instrument, the counseling questionnaire, the clinic-based survey instrument, the home-based survey instrument, and the phone survey instrument are provided in Multimedia Appendix 2. Baseline surveys were administered in a private room in the woman’s place of residence and lasted approximately 2 hours. Short breaks of 5 to 10 minutes were given to the respondents at the end of each section, and additional breaks were taken at the request of the participant and at other scheduled times (eg, mealtime and picking up children from school) as needed. Surveys were conducted in Chichewa, the local language, and strictly follow the format of the questionnaires, which were electronically programmed into Android tablets. To successfully track our participants over time, we collected identifiable data, including names and contact information, names and background characteristics of other household members, household addresses, contact phone numbers and emails, and GPS coordinates of the household. For the purposes of minimizing loss to follow-up, we took photographs of the household and of the survey respondents, and we asked respondents to provide the names and contact information of 2 contacts who did not live in the household and who could be contacted if the respondents could not be directly located in the follow-up period. To protect participant privacy and ensure confidentiality, all identifiable data are appropriately stored and secured in accordance with the data security measures described in the Data Safety and Monitoring section below.

### Analysis Plan

The analysis of quantitative study data will be conducted using STATA and R (R Foundation), where appropriate. Descriptive analysis will be performed for all variables, and unadjusted comparisons between experimental arms will be conducted. Descriptive statistics, including frequencies, means, and SDs, will also be performed. Chi-square tests and one-tailed *t* tests will be used to examine associations in the data. A probability value of less than .05 will be considered statistically significant for all the statistical tests that are conducted. Continuous variables will be tested for normality, and nonnormal values will be categorized or appropriately transformed. Given our hypotheses regarding the impact of our intervention on our key outcomes, one-sided hypothesis tests will be conducted for all our main analyses.

Our main econometric specifications will (1) estimate the intent-to-treat (ITT) effects of our family planning intervention on fertility intentions and preferences, contraceptive intentions and preferences, intention to switch methods, and other outcomes related to contraceptive behaviors by directly regressing our outcomes of interest on a binary variable indicating receipt of the intervention and (2) estimate the effect of interventions on downstream behavioral outcomes (such as women’s uptake of contraceptive options and the concordance between their revealed preference and their stated preference) using a 2-stage least squares model, in which the intermediate counseling variable will be instrumented by the treatment. The main econometric specification for estimating the ITT effect of our family planning intervention is defined as follows:

*Y_it_* = *β_0_* + *β_1_T_it_* + *X_it_ζ* + *Y_i0_* + *η_i_* + *ε_it_*

where *Y_it_* is the outcome variable of interest for woman 𝑖 in time period 𝑡=0, 1, 2 for baseline (time period 0) and follow-up (time periods 1 and 2), respectively; *T_it_* is an indicator of assignment to 1 of the 3 treatment arms; *X_it_* is a vector of individual-level covariates that are controlled for in the analysis; η_i_ is the individual-specific fixed effect; *Y_i0_* is the baseline level of the outcome; and *ε_it_* is the error term. Here, the outcome variables of interest include immediate, intermediate, and long-term outcomes described in the previous sections.

We will conduct several subgroup analyses to examine how our family planning intervention effects vary across key subpopulations. Subgroups of interest include women who have or do not have their husbands’ approval for accessing contraceptive methods, women who have or have not previously used family planning methods, women whose most valued method attribute is or is not effective, working or nonworking women, higher or lower educated women, counseling sessions administered in the morning or afternoon, women who have more or less than 2 children, and counseling sessions of above or below the median length.

Finally, robustness checks (5% and 10% sample truncations and coarsening of independent variables) and falsification tests, which include placebo regression, simulation, and resampling methods, will be conducted to ascertain the strength and significance of our estimates. We will also conduct attrition-adjusted analyses to assess the extent of differential loss-to-follow-up on outcomes. In handling missing data, we will conduct a complete case analysis if the potential impact of the missing data is negligible, and we can conduct a series of sensitivity analyses, including *best-worst* case analyses, to generate plausible bounds of estimates across different scenarios of missingness. If we are able to assume that any missing data are missing at random, then we will conduct an ITT analysis using multiple imputation to adjust for missing data. We will then compare the ITT estimates from our multiple imputation analysis with our estimates from a complete case analysis, which would allow us to infer the extent to which missingness might impact our inference.

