### Sample Size and Power Calculations

#### Target Sample and Key Outcomes

The sample size of this study was powered to primarily identify the independent effects of tailored family counseling and male involvement on women’s contraceptive uptake and switching of methods. On the basis of the preliminary power calculations for the primary outcomes of interest, our target baseline sample consists of 700 eligible women who consent to participate in the study. Among these 700 women, 100 women were assigned to the control arm T0, and 200 women were assigned to each of the 3 intervention arms, namely, T1, T2, and T3.

Previous studies have found that one-fifth of women of reproductive age were either pregnant or had given birth to a child in the past 6 months [40]. To meet our target sample size of 700 women who would be eligible to participate in our study, we need to recruit a total of 940 women if we conservatively assumed a combined ineligibility or refusal rate of 25%.

We have powered our study to detect effects on the following outcomes: (1) contraceptive uptake and (2) intention to switch from the current contraceptive method.

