#### Contraceptive Prevalence: Partner Invitation Interventions

Using modern contraceptive prevalence estimates for urban area of Malawi from the 2010 Malawi DHS, we assume a modern contraceptive prevalence rate of 50% among women aged 18-35 years who are currently not pregnant and who did not give birth in the 6 months before the baseline. To infer a potential effect size for our intervention, we look to evidence to a study from Zambia [28], which found that male involvement in family planning care-seeking decreased the probability of receiving family planning services by 19% over a 2-year study period. Our study differs from this study in that we do not require husbands to participate in the counseling session; instead, we leave it up to the woman to decide whether she would like to invite her husband to counseling or not. In designing our invitation in this way, a selection effect might exist, in which husbands who are more supportive of contraceptive use are more likely to comply with the intervention and participate in a joint counseling session. As a result, our male partner invitation intervention would likely lead to an increase in contraceptive prevalence.

Assuming an attrition-adjusted sample of 700 women, with 400 women assigned to partner invitation arms, T1 and T3, compared with 300 women assigned to noninvitation arms, T0 and T2, we will have 75% power to detect a percentage point increase of 10 in the contraceptive prevalence rate from 50% to 60% (α=.05, two-sided). If, instead, we use a one-sided test, then we estimate that we would have 85% power to detect the same 10 percentage point increase in contraceptive prevalence.

Table 4 presents the levels of power (1−β) that could be achieved for various minimum effect sizes for the modern contraceptive prevalence use, assuming a baseline contraceptive prevalence rate of 50% in both the intervention and control arms and a fixed endline sample size of 700 women.

**Table 4 table4:** Power calculations for contraceptive prevalence rate, partner invitation intervention.

Control CPR^a^, n (%)	Intervention CPR, n (%)	Significance level, α	Control sample size, n	Intervention sample size, n	Power
150 (50)	236 (59)	.05	300	400	0.66
150 (50)	240 (60)	.05	300	400	0.75
150 (50)	244 (61)	.05	300	400	0.83
150 (50)	248 (62)	.05	300	400	0.89

^a^CPR: contraceptive prevalence rate.

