#### Intention to Switch Methods: Partner Invitation Interventions

Our measure of a woman’s intention to switch to another contraceptive method is proxied by her answer to the question, “if you had the choice and ability to switch to another family planning method, would you choose to switch?” An intervention to encourage women to invite their husbands or male partners to counseling could have 2 potential effects on women’s stated preferences for family planning methods. On the one hand, male involvement in counseling may encourage women to change their contraceptive preferences by allowing women to more actively retain and interpret counseling messaging [15,16] and through increased communication between partners [20]. On the other hand, male involvement in counseling might discourage women from changing their stated preferences if they feel compelled to hide their true preferences from their partners [41]. On the basis of the existing evidence on male involvement, we hypothesize that male involvement in counseling is likely to increase a woman’s intention to switch methods. Assuming an attrition-adjusted sample of 700 women, with 400 women assigned to partner invitation arms, T1 and T3, compared with 300 women assigned to noninvitation arms, T0 and T2, we will have 86% power to detect a 10 percentage point increase in women’s intention to switch methods in the intervention arm from 20% to 30% (α=.05, two-sided). If, instead, we use a one-sided test, then we estimate that we would have 92% power to detect the same 10 percentage point increase in intentions to switch.

Table 5 presents the levels of power (1−β) that could be achieved for various minimum effect sizes for the likelihood of women’s intention to switch contraceptive methods, assuming a baseline switching rate of 20% in both the intervention and control arms and a fixed endline sample size of 700 women.

**Table 5 table5:** Power calculations for intentions to switch methods, partner invitation intervention.

Control likelihood, n (%)	Intervention likelihood, n (%)	Significance level, α	Control sample size, n	Intervention sample size, n	Power
60 (20)	112 (28)	.05	300	400	0.69
60 (20)	116 (29)	.05	300	400	0.78
60 (20)	120 (30)	.05	300	400	0.86
60 (20)	124 (31)	.05	300	400	0.91

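### A normality pre-test, followed by an open choice between categorizing and transforming, makes the form of numeric outcomes depend on the trial data for no statistical gain

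*Protocol article*

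**What the plan says.** The first paragraph of the Analysis Plan states: "Continuous variables will be tested for normality, and nonnormal values will be categorized or appropriately transformed". It separates neither outcomes from covariates nor primary from secondary variables, and it offers two remedies after a failed test without saying which applies.

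The same paragraph sets the testing basis: "A probability value of less than .05 will be considered statistically significant for all the statistical tests that are conducted", and "one-sided hypothesis tests will be conducted for all our main analyses". The planned tools are chi-square tests, one-tailed t tests, linear ITT regression and two-stage least squares.

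Primary Outcomes includes numeric items, for example use of local health facilities, "including the frequency of visits to local clinics". It also lists knowledge, autonomy and empowerment, which may or may not be scored numerically. Target Sample and Key Outcomes names the powered outcomes as "1) contraceptive uptake and (2) intention to switch from the current contraceptive method". Both are binary.

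The coarsening of independent variables later in the Analysis Plan is a separate robustness check and does not alter this rule.

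**The concern.** This is a stated instruction, not a detail left to an unseen analysis plan. Three features make it a poor one.

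- **It answers a question the analysis does not ask.** Comparisons of means and linear regression at this size do not require the variable itself to be normal.
- **It will trigger for most survey measures.** Large-sample normality tests reject for departures that do not matter.
- **It changes what is estimated.** A difference in mean visits, a ratio on a log scale and a difference in the proportion above a cut point are different effects. Under this rule, which one is reported depends on the trial's own data and on a choice the text leaves open.

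At stake are the interpretability of the numeric outcomes and, if categorizing is chosen, possibly their power.

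**Working it through.** **1. The plan's own power figures.** Inputs: "with 400 women assigned to partner invitation arms, T1 and T3, compared with 300 women assigned to noninvitation arms, T0 and T2", with "75% power to detect a percentage point increase of 10 in the contraceptive prevalence rate from 50% to 60% (α=.05, two-sided". The pooled proportion is (150 + 240)/700 = 0.557. The null SE is √[0.557 × 0.443 × (1/300 + 1/400)] = 0.0379, and the alternative SE is √(0.25/300 + 0.24/400) = 0.0379. Power = Φ[(0.10 − 1.96 × 0.0379)/0.0379] = Φ(0.677) = 0.751, which matches 0.75. The same formula for "86% power to detect a 10 percentage point increase in women’s intention to switch methods in the intervention arm from 20% to 30"% gives 0.856, which matches 0.86. All rows of Tables 4 to 7 reproduce. These outcomes are binary, so the rule does not touch them.

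**2. How readily the rule triggers.** The article names no test, so Shapiro-Wilk is assumed. With n = 731 completers and 1,000 simulated samples per case, rejection at 0.05 was:

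| Distribution | Rejected |
|---|---|
| Normal | 5% |
| Gamma, skewness 0.25 | 69% |
| Gamma, skewness 0.5 | 100% |
| Integer score 0 to 20 (binomial) | 100% |

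**3. Whether the test is needed.** Simulated one-sided type I error of the t test at 300 against 400 (5,000 runs, nominal 0.05) was 0.046 for lognormal data (σ = 1) and 0.054 for exponential data. The level holds without normality.

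**4. Loss from categorizing a roughly normal variable.** This is an illustration, because the article powers no continuous outcome and names no cut point. A median split keeps 2/π = 0.637 of the information, and √0.637 = 0.798. One-sided power is Φ[(1.645 + z) × 0.798 − 1.645], where z is the normal quantile of the starting power:

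- 80% (z = 0.842): Φ(0.339) = 0.63
- 90% (z = 1.282): Φ(0.690) = 0.75

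Starting from 80%, tertiles give 72% and quartiles 75%.

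**5. Loss for a count.** Assume Poisson visit counts with means 0.80 (300 women) and 0.98 (400 women).

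- Kept as counts: SE = √(0.80/300 + 0.98/400) = 0.0715, so power is Φ(0.18/0.0715 − 1.645) = Φ(0.87) = 0.81.
- Any visit against none: the proportions are 1 − e^−0.80 = 0.551 and 1 − e^−0.98 = 0.625. The pooled SE is 0.0375, so power is Φ(0.074/0.0375 − 1.645) = Φ(0.33) = 0.63.

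**6. Strongly skewed data.** For lognormal data with a multiplicative effect, the efficiency of a median split relative to the raw-scale mean is (2/π)(e^σ² − 1)/σ²:

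| σ | Split against raw mean | Split against log scale |
|---|---|---|
| 0.5 | 0.72 | 0.64 |
| 1.0 | 1.09 | 0.64 |
| 1.5 | 2.40 | 0.64 |

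The split can equal or beat the raw mean. It never beats the log scale here.

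**The case against.** **Categorizing is only one of two options.** True. The power loss follows only if it is chosen. The dependence of the form on the data remains either way.

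**The usual information-loss figure assumes near-normality, but the rule acts on nonnormal variables.** This stands. A reader might infer that the plan throws away about 36% of its information, so that 731 completers act like about 465 (731 × 0.637). The article does not support that as the cost of the rule: it does not commit to categorizing, names no cut point, and for strongly skewed data the comparison with the raw scale can reverse (step 6).

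**Few important outcomes are affected.** Largely right. The powered outcomes are binary. Parity and months since last birth can hardly respond, since women were not pregnant at screening and follow-up comes after a 1-month service period. Visit frequency remains, as does any knowledge or empowerment measure that is scored.

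**The sentence may govern only descriptive comparisons.** Its paragraph opens with descriptive work, but the same paragraph sets the significance level for all tests and the sidedness of the main analyses. Nothing limits the rule to description.

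**Post hoc choice is inferred.** A reader might infer that the form will be picked by result. If it were picked as the best of raw, log and median split, simulated one-sided type I error for lognormal data would be about 0.105. The article does not say this will happen, cut points may be set in a document not shown, and a normality check on pooled data uses no arm labels and need not inflate error. It is a risk that the text permits, not one that it states.

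**Conclusion.** The point holds in a limited form. The article states a normality pre-test that its methods do not need and that would fail most survey measures at this sample size. It then leaves the form, and so the effect scale, of numeric outcomes to an open choice. This reaches at least one listed primary outcome, clinic-visit frequency.

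No single figure describes the cost. If a median split is used, one-sided power falls from 80% to about 63% for a roughly normal variable, and from 81% to 63% in the count example. For strongly skewed data the loss against the raw scale may vanish or reverse. These figures rest on assumed distributions, starting powers and cut points. The simulation of how often the rule triggers assumes Shapiro-Wilk. The stated power for the two powered outcomes is untouched.

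**What to change.** Delete the sentence on normality testing and categorization. In its place:

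- Analyze numeric outcomes uncategorized, by linear regression with robust standard errors, or by Poisson regression with robust standard errors for counts.
- For outcomes expected to be clearly skewed, name any transformation in advance, on substantive grounds, before results by arm are examined. The article reports the primary analyses as under way, so record when each form was fixed.
- Use categories for description only.

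The cost is analysis wording, with no new data and no change in conduct. There is one small downside: for very skewed outcomes the raw-scale mean can be less precise, which a prespecified transformation addresses.

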
### Study Objectives

In this study, we identified the causal impact of user-centered approaches to family planning counseling on women’s contraceptive preferences and decision making by means of a randomized controlled trial. In particular, we investigated two channels that have been hypothesized to play a role in contraceptive decision making: (1) a preference-based, targeted, user-centered approach to family planning counseling and (2) male involvement in family planning counseling. To this end, we tested the following 2 hypotheses:

A preference-driven, tailored, user-centered approach to counseling would allow women to express and realize their contraceptive preferences more effectively.The involvement of male partners in family planning counseling may allow women to express their contraceptive preferences and, in turn, translate their preferences into behavior more effectively.

The study population comprised married women aged 18-35 years living in Lilongwe, Malawi. As part of the trial, each woman in the study was randomly assigned to 1 of the 3 treatment arms or a control arm. A woman assigned to one of the intervention arms received one tailored, user-centered counseling session, followed by a package of family planning services that was designed to reduce the key barriers to accessing family planning in urban Malawi. The primary objective of this study is to evaluate the impact of user-centered counseling on a woman’s contraceptive use, intention to change stated ideal methods, switching of the current method, and realization of the stated ideal method. Primary outcomes include changes to women’s contraceptive method preferences (both stated and realized) over time and changes to women’s contraceptive concordance (whether a woman’s stated choice of contraceptive method, her ideal method, is the method that she is, in fact, using). Secondary outcomes include changes to male partners’ fertility and family planning preferences, women’s sexual and marital well-being, and changes in women’s decision-making in the household.

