### Study Limitations

Our study has several limitations. Although the study is powered to independently test the effects of 2 user-centered counseling procedures on women’s stated and realized preferences, the sample size of this study may be too small to allow for the examination of interaction effects across treatment arms. As an exploratory exercise, we will examine these effects and present them as supplementary findings. Moreover, although our study can infer the manner in which women realize their preferences in response to counseling, it is not as straightforward to be able to disentangle a woman’s true individual preferences for family planning from her stated preferences in the presence of her partner, who is likely to influence her eventually realized choice (or lack of choice) of method. To this end, additional research is warranted to better understand how women’s true preferences are expressed and can be documented, even in cases where their partner is present. Similarly, it would be equally necessary to further explore the trade-off that women face between (1) making independent decisions to reflect their individual preferences and (2) incorporating their husband’s/family’s preferences to make jointly/socially better-off, but not necessarily individually better-off, decisions.

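### As written, the main ITT regression has one pooled treatment term (any of T1–T3 versus T0), which estimates neither hypothesised effect and is not the 400-versus-300 contrast that was powered

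*Protocol article*

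**What the plan says.** Study Objectives states two separate hypotheses. The first is that "A preference-driven, tailored, user-centered approach to counseling would allow women to express and realize their contraceptive preferences more effectively". The second begins "The involvement of male partners in family planning counseling may allow women to express their contraceptive preferences". Target Sample and Key Outcomes says the sample was "powered to primarily identify the independent effects of tailored family counseling and male involvement". Study Limitations repeats that "the study is powered to independently test the effects of 2 user-centered counseling procedures" and leaves only the interaction as exploratory.

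The power sections treat each effect as one margin of a 2×2 design. For invitation the comparison is "400 women assigned to partner invitation arms, T1 and T3, compared with 300 women assigned to noninvitation arms, T0 and T2". For targeting it is T2 and T3 (400) against T0 and T1 (300).

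The Analysis Plan gives a different model. The main ITT effects are obtained "by directly regressing our outcomes of interest on a binary variable indicating receipt of the intervention". The equation has one coefficient β1 on T, and T "is an indicator of assignment to 1 of the 3 treatment arms". Downstream outcomes such as uptake and concordance use two-stage least squares, "in which the intermediate counseling variable will be instrumented by the treatment". One-sided tests at .05 are specified for all main analyses. The article writes out no regression with separate invitation and targeting terms.

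**The concern.** A single binary term with a single coefficient merges three arms that received different things: husband invitation only (T1), targeted content only (T2), and both (T3). The coefficient is then a blend of the two effects the study set out to separate. A positive result could not be attributed to either intervention, and a null result could hide one effective intervention or two opposed ones. The comparison also rests on a control arm of 100 rather than 300, so the stated power does not belong to it.

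The text also calls the treatment variable receipt in one sentence and assignment in the next. Only assignment gives an ITT estimate.

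**Working it through.** **Inputs.** Planned arm sizes are T0 = 100 and T1 = T2 = T3 = 200 (Randomization; Target Sample and Key Outcomes). Contraceptive use goes from 50% to 60% and intention to switch from 20% to 30%, at α = .05 (power sections). The 700 women are already attrition-adjusted.

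**Formula.** Power = Φ[(d − z·SE₀)/SE₁]. SE₀ is the pooled-null standard error, SE₁ the unpooled one, and there is no continuity correction. z is 1.960 two-sided and 1.645 one-sided.

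**Step 1: reproduce the plan's figures (400 v 300).** For use, the pooled proportion is (300×0.50 + 400×0.60)/700 = 0.557, and SE₀ and SE₁ are both 0.0379.
- Two-sided: (0.10 − 1.960×0.0379)/0.0379 = 0.68, power 75.1% (stated 75%).
- One-sided: 84.0% (stated 85%).
- Switching: 85.6% two-sided (stated 86%) and 91.7% one-sided (stated 92%).

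The power figures are therefore right for the contrasts they describe.

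**Step 2: the contrast in the written equation (600 v 100), same 10-point difference.** For use, SE₀ = 0.0532 and SE₁ = 0.0539. One-sided, (0.10 − 1.645×0.0532)/0.0539 = 0.23.

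| Outcome | One-sided, 600 v 100 | Stated | Two-sided, 600 v 100 | Stated |
|---|---|---|---|---|
| Use | 59% | 85% | 47% | 75% |
| Switching | 67% | 92% | 54% | 86% |

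**Step 3: what β1 estimates.** Let a be the invitation effect and b the targeting effect, assumed additive. Relative to T0, the arm effects are a (T1), b (T2) and a + b (T3). Then β1 = [200a + 200b + 200(a + b)]/600 = (2/3)a + (2/3)b.

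| a, b (points) | Expected β1 | Power for use, one-sided / two-sided | Power for switching, one-sided / two-sided |
|---|---|---|---|
| +10, 0 or 0, +10 | 6.7 | 34% / 24% | 40% / 28% |
| +10, +10 | 13.3 | 81% / 71% | 87% / 79% |
| +10, −10 | 0 | none | none |

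**Step 4: are simple 400-v-300 margins a clean substitute?** Not quite. Among invited women, 200/400 = 50% get targeted counseling. Among non-invited women, 200/300 = 67% do. The invitation margin therefore estimates a + (1/2 − 2/3)b = a − b/6, and by symmetry the targeting margin estimates b − a/6. A 10-point effect of the other factor shifts a margin by −1.7 points.

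**Step 5: both indicators in one model.** Least squares on arm sizes 100/200/200/200, with binomial variances and additive effects, is unbiased for a and b. The standard errors are 0.0374–0.0384 for use and 0.0330–0.0351 for switching; the range covers one or both factors working. Power = Φ(0.10/SE − z).
- Use: 83–85% one-sided, 74–76% two-sided.
- Switching: 89–92% one-sided, 81–86% two-sided.

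**The case against.** The strongest reply is that the equation is a template, with T standing for each factor in turn. The power tables label the 400 women as intervention and the 300 as control, factor by factor, and the limitations section plainly expects two main effects. A condensed article may also leave the exact coding to a fuller plan. This supports the view that the investigators intend two effects. It does not rescue the text, which defines T by assignment to one of three treatment arms and gives it one coefficient. Fitting the template one factor at a time would also leave the −1/6 carry-over of Step 4.

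A second reading is one dummy per arm. Each comparison is then 200 versus 100, with 50% one-sided (38% two-sided) power for a 10-point difference in use. That is not the powered contrast either.

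It is also fair to say that the pooled test does well when both interventions work, and that the plan expects invitation to raise use, so exact cancellation is not its expectation. Both points stand, and the 13.3-point case is shown for that reason. Attribution remains impossible even then. The protocol itself cites a Zambian study in which male involvement reduced receipt of services, and it concedes that invitation could move switching intentions either way.

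A reader might go further on three points, and the documents do not support any of them.
- **The two-stage least squares estimates are invalid by construction, with a bias of known size.** The intermediate counseling variable is not defined, so neither claim can be shown.
- **The plan assumes +10 points for both interventions at once.** Each calculation is made separately, and the targeting figure is described as an assumed minimum detectable effect.
- **The trial cannot answer its hypotheses.** The design and data can; the written model does not.

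**Conclusion.** The point holds for the model as written. A single pooled treatment term estimates two thirds of the sum of the two effects, not either one, and its 600-versus-100 comparison has 59% one-sided power for use and 67% for switching at 10 points, where the plan states 85% and 92%. The blend formula rests on additive effects and planned arm sizes. The power figures ignore covariates, the baseline outcome and stratification, which may change precision but do not turn β1 into either factor effect.

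The carry-over in the simple margins is real but modest. Receipt versus assignment is a wording conflict, since the analysis is labelled ITT. For the two-stage analysis the supportable statement is limited: a single pooled treatment is an unsuitable instrument, because the arms shift different things (husband involvement, counseling content, or both).

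**What to change.** Replace the single T with two indicators defined by assignment and fitted in the same model: Y = β0 + β_I·Invited (T1, T3) + β_T·Targeted (T2, T3) + the remaining terms already planned. Test β_I and β_T as the two main effects. Keep Invited×Targeted as the exploratory term that Study Limitations already promises. Change receipt to assignment in the ITT sentence.

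For two-stage least squares, name the intermediate variable, use the matching factor as its instrument, and control for the other factor.

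The cost is wording in the analysis plan, with no extra data or participants. The article reports the analysis as ongoing, so the change should be dated and recorded as made before or after results were seen.
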